#### Analysis related to the primary objective

We hypothesize that the proportion of patients with new CMBs and/or cSS on end-study MRI will be higher in the continuation arm. This hypothesis will be tested via a logistic regression model relating the presence of new lesions to treatment assignment.

#### Analyses related to the secondary aims

In order to explore whether the presence and burden (number) of CMBs on baseline MRI can be used as an imaging marker to stratify the risk/benefit of statin therapy, a proportional hazards model will be used to relate the time to symptomatic ICH recurrence to treatment assignment, the presence and burden of CMBs/cSS, and the corresponding interaction. The interaction term will be used to evaluate the heterogeneity of the treatment effect according to presence/burden, and the corresponding treatment effects and 95% confidence intervals will be constructed. The effects of statin continuation on the incidence of new ischemic MRI markers (WMH and covert infarcts) on end-study MRI will be evaluated via logistic regression model relating the presence of new markers to treatment assignment. Heterogeneity of the treatment effect across racial/ethnic subgroups will be explored by extending the proportional hazards model to include main effects for sex and racial/ethnic subgroups and their corresponding interactions with treatment and presence/number of new lesions.

The association between the incidence of new MRI markers on end-study MRI and deterioration of cognitive function, quantified by T-MoCA, and functional outcome, quantified by mRS, will be evaluated. As in the parent trial, the T-MoCA will be analyzed by considering cognitive decline (reduction of at least two points from the highest score to any subsequent assessment), as well as normal cognition (T-MoCA ≥ 20); the mRS will be dichotomized (0–3 vs 4–6). A generalized linear mixed effects model will be constructed for each outcome independently in order to relate outcome to treatment, time, and presence of new lesions; in addition to the adjustments for randomization covariates specified above, the models will include an indicator for baseline cognitive decline/dementia derived from the subject’s medical history.

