## Introduction

A large percentage of spontaneous intracerebral hemorrhage (ICH) is caused by cerebral small vessel disease (CSVD) [1, 2], either hypertensive arteriopathy (arteriolosclerosis)—associated with non-lobar—or cerebral amyloid angiopathy (CAA), linked to lobar hemorrhages. There are several imaging markers of CSVD such as cerebral microbleeds (CMBs), cortical superficial siderosis (cSS), lacunes, white matter hyperintensities (WMH), and enlarged perivascular spaces (PVS) which can be identified using MRI. The presence and severity of CMBs and cSS in particular have been associated with an increased risk of first ICH and ICH recurrence in patients with CAA [3–5].

Patients with spontaneous lobar ICH often have varying degrees of underlying CSVD on MRI, and the effects of long-term statin therapy on the burden of CSVD have yet to be defined. There is evidence that statin use is independently associated with the presence and increased number of CMBs, especially in cortical locations [6–8] and that statin treatment can reduce incident covert brain infarcts [9]. Determining the association of statin therapy with accrual of CSVD is important, as the accumulation of microvascular insults potentiates vascular cognitive impairment, functional decline, and gait impairment in older age [10–12]. The presence and burden of CSVD markers, in particular CMBs and cSS, may additionally be useful as a screening tool to stratify the benefit-risk of statin therapy in ICH survivors taking statins and to monitor the effects of statins on the progression of these markers and potentially increased propensity to recurrent ICH. Many physicians take these imaging features into consideration to guide their therapeutic decisions in patients with ICH [13]. However, evidence from randomized controlled trials (RCTs) supporting the prognostic value of these imaging features in ICH patients is lacking.

The SATURN-MRI ancillary study provides a synergistic opportunity to examine the prognostic and pathophysiological characteristics of MRI biomarkers of CSVD within the scope of a large-scale, prospective RCT.

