#### Secondary objectives

To assess whether the presence and burden of CMBs and cSS on baseline MRI modifies the effects of statin on the risk of recurrent symptomatic ICH and can potentially be used as an imaging marker to stratify the benefit-risk of statin therapy in patients with lobar ICH. We also aim to examine the modifying effects of these markers on the risk of MACCE.To evaluate the effects of statin continuation vs. discontinuation on the incidence of new ischemic MRI markers (white matter hyperintensities (WMH) and covert infarcts) on end-study MRI.To evaluate interactions between statin continuation vs. discontinuation, accrual of MRI markers of CSVD, and functional and cognitive outcomes at the end of the study at 24 months.

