The SATURN trial is limiting eligibility to lobar ICH as a pragmatic means of deriving a CAA-enriched population. However, not all spontaneous lobar ICH are due to CAA in older populations, with a proportion resulting from underlying hypertensive arteriopathy [32]. The use of MRI would further help to improve the diagnosis of CAA through the use of the clinico-radiographic Boston Criteria. Moreover, even within CAA cohorts, response to stroke preventive treatments has been shown to differ depending on the severity of underlying disease manifested by MRI biomarkers [33]. MRI would allow assessment of treatment interactions between baseline MRI phenotypes suggestive of advanced CAA (which might be at greatest risk for increased recurrent ICH with continued statin therapy) and statin continuation vs. discontinuation. The potential to use MRI markers, such as CMBs and cSS, to identify patients who benefit or are harmed from long-term statin therapy could facilitate individualized decision-making and risk stratification and would be an important and novel contribution to the field which could have important cost- and resource-saving implications. In practice, the results of SATURN MRI will be interpreted in concert with those of the main SATURN trial. An increased risk of ICH recurrence with statin continuation in the SATURN main trial and as well an increased risk of ICH recurrence in patients with CMBs/cSS on baseline MRI in SATURN MRI would indicate higher absolute risks of ICH recurrence and lower numbers needed to harm in patients with CMBs/cSS. Conversely, if SATURN main results do not show an increased risk of ICH recurrence with statin continuation, but SATURN MRI shows increased risk in patients with CMBs/cSS, the results can similarly lead to individualization of treatment decisions according to MRI phenotypes. However, if both SATURN and SATURN MRI do not show increased risk of ICH recurrence with statin continuation, this would provide reassurance supporting the safety of statins among the highest risk subgroups of lobar ICH patients and could lead to avoidance of unnecessary neuroimaging in clinical practice and hence save costs.

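### Whether baseline CMBs/cSS modify the statin effect on recurrent ICH is judged on the hazard-ratio scale, but the aim and the Discussion need absolute risks by marker, which no stated analysis estimates

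*Protocol article*

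**What the plan says.** Under Secondary objectives, the article asks whether CMBs and cSS at baseline modify the statin effect on recurrent symptomatic ICH, and whether they "can potentially be used as an imaging marker to stratify the benefit-risk of statin therapy in patients with lobar ICH". Modification of the effect on MACCE is part of the same objective.

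Under Analyses related to the secondary aims, "a proportional hazards model will be used to relate the time to symptomatic ICH recurrence to treatment assignment", to the marker, and to their product. The criterion is then fixed: "The interaction term will be used to evaluate the heterogeneity of the treatment effect according to presence/burden". The sentence goes on to say that "the corresponding treatment effects and 95% confidence intervals will be constructed", without naming their scale. The section gives no model for modification of the MACCE effect.

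The Discussion says that raised recurrence with statins in the main trial, together with raised recurrence in marker-positive patients, "would indicate higher absolute risks of ICH recurrence and lower numbers needed to harm in patients with CMBs/cSS".

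On baseline risk by marker, the Introduction gives a direction but no size: "The presence and severity of CMBs and cSS in particular have been associated with an increased risk of first ICH and ICH recurrence".

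**The concern.** A number needed to harm is the reciprocal of a risk difference, and a benefit-risk judgement for a marker-defined group rests on absolute risks. The product term of a proportional hazards model asks something else: whether the hazard ratio differs by marker. The two questions have different answers whenever the marker shifts baseline risk and the hazard ratio is not 1. The article holds the first condition to be true and takes a hazard ratio of 1.68 as its working statin effect.

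At stake is how a null interaction is read. Without a stated absolute-scale estimate, it could be taken to mean that CMBs/cSS do not help to stratify benefit-risk, although absolute harm differs materially between the groups. If the absolute scale is brought in only after the results are known, the choice of scale is open to the charge of being data-driven.

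**Working it through.** **Plan's own figure.** The article states no recurrence rate, event count or power for the interaction analysis, so there is nothing to reproduce for it. Its one sample size concerns the imaging outcome (12% vs 20%, 80% power, 652 subjects). A two-sided 5% normal approximation gives 658, with 79.7% power at 652. That agrees, but does not bear on this point.

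**Inputs.**
- Hazard ratio 1.68, from Sample size calculations. There it is an ICH result from an earlier statin trial, borrowed for the imaging outcome. I also use 1.3 and 2.0 as assumptions.
- 24-month recurrence risk under discontinuation: not given. Assumed 2% to 5% without the marker, and 2, 3 or 4 times that with it.
- Marker prevalence 57%, from Sample size calculations. This is for CMBs alone; I use it for marker presence.
- N = 894, 1:1 allocation.

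**Step 1: the same hazard ratio in both strata.** With discontinuation risk r, the risk under continuation is 1 − (1 − r)^HR, and the risk difference is that minus r. The ratio of hazard ratios is exactly 1.00 in every row. With HR 1.68:

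| r without / with marker | Risk difference, points | NNH | Ratio of differences |
|---|---|---|---|
| 3% / 6% | 2.0 / 3.9 | 50 / 26 | 1.95 |
| 3% / 9% | 2.0 / 5.7 | 50 / 18 | 2.84 |
| 4% / 12% | 2.6 / 7.3 | 38 / 14 | 2.79 |
| 4% / 16% | 2.6 / 9.4 | 38 / 11 | 3.57 |

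For 4% / 12%: 1 − 0.96^1.68 = 0.0663 and 1 − 0.88^1.68 = 0.1933, so the differences are 0.0263 and 0.0733.

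**Step 2: range.** Over HR 1.3, 1.68 and 2.0, the ratio of risk differences is:
- 2-fold baseline ratio (2/4%, 3/6%, 5/10%): 1.89 to 1.97
- 3-fold (3/9%, 4/12%, 5/15%): 2.68 to 2.88
- 4-fold (4/16%, 5/20%): 3.37 to 3.66

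The ratio of absolute harms stays slightly below the assumed ratio of baseline risks.

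**Step 3: precision.** Take 3% / 9%, HR 1.68, N = 894, all followed to 24 months. There are 894 × 0.43 / 2 = 192 per arm without the marker and 894 × 0.57 / 2 = 255 per arm with it. The risks are 3.0% and 5.0%, and 9.0% and 14.7%.
- Between-stratum contrast: 5.65 − 1.99 = 3.7 points.
- Standard error: the square root of the four terms p(1 − p)/n summed = 0.0348, about 3.5 points.
- Power of a two-sided 5% test: Φ(0.0366/0.0348 − 1.96) = 18%.
- On the relative scale, expected events are 5.8, 9.6, 22.9 and 37.3. The standard error of the log ratio of hazard ratios is √(1/5.8 + 1/9.6 + 1/22.9 + 1/37.3) = 0.59. The ratio detectable with 80% power is exp(2.8 × 0.59), about 5.2.

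Under these assumptions neither interaction test is sensitive. That is a further reason not to let a null result on one scale stand for the benefit-risk conclusion.

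**The case against.** The case against has real force.

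The Cox interaction is a standard, valid assessment of effect modification, and the objective names no scale. A reader might infer that the planned test is wrong or does not address the objective. The article does not support that: the test answers the relative-scale form of the question.

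The plan also promises treatment effects with confidence intervals, and a model with treatment, marker and their product can yield 24-month risks. A condensed article may leave such detail to an analysis plan. This is why the point is not that output is missing. It is that the article fixes one relative-scale criterion and then describes conclusions on the absolute scale, with no stated estimate linking them.

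A reader might also infer that a marker separating large from small absolute harm would certainly be reported as not modifying the effect. The Discussion tells against this. The first of its scenarios requires no hazard-ratio interaction and already reads raised risk in both respects as a lower number needed to harm. The authors see the point; what they lack is a stated estimate to carry it.

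Three further readings go too far:
- A single headline figure such as a threefold difference in harm. It only returns the baseline ratio put in, and the article gives direction alone.
- A reversal of direction. Hazard ratios of 2.0 at 4% and 1.4 at 12% give 3.8 vs 4.4 points, but that 0.6-point gap needs two more assumed hazard ratios and is small beside a standard error of about 3.5 points.
- That MACCE modification will be judged only by a hazard-ratio interaction. The article states no model for it.

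Finally, making a formal additive test the lead result would be poorly powered. That stands, and the fix is limited to estimation.

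**Conclusion.** The concern holds as a mismatch of scale, not as an error in the model. For recurrent ICH, the stated criterion is relative, the aim is to stratify benefit-risk, and the Discussion draws conclusions on absolute risk and number needed to harm that no stated analysis estimates. With a truly null hazard-ratio interaction, absolute harm would differ about 1.9- to 3.7-fold by marker. That size rests on assumed 2- to 4-fold baseline risk ratios, marker-negative 24-month risks of 2% to 5%, and a common hazard ratio between 1.3 and 2.0. None of the recurrence risks comes from the article. The qualitative conclusion needs only that the marker raises recurrence risk, that the hazard ratio differs from 1, and that risks are of this low order. It is a cheap improvement worth making before results are known.

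**What to change.** In Analyses related to the secondary aims:

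1. Keep the hazard-ratio interaction as the relative-scale result.
2. Add, as estimation and not as a decisive test, the 24-month risk of recurrent ICH by arm and by marker presence or absence. Give the risk difference in each stratum, the contrast between strata, and 95% confidence intervals. Presence or absence is enough; the burden categories would thin the cells.
3. Account for death as a competing event and stay consistent with the covariate adjustment set out under Data analyses, for example by standardising risks from adjusted cause-specific models.
4. Do the same separately for MACCE, treating death as competing where it is not part of that endpoint.
5. State that a null hazard-ratio interaction will not by itself be read as equal benefit-risk, and tie the number-needed-to-harm statements in the Discussion to these estimates.

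This changes wording and adds one set of estimates from data already being collected. The cost is wide intervals: at assumed risks of 3% and 9%, a contrast of 3.7 points would carry a standard error of about 3.5 points, so the text should say in advance that the contrast is descriptive.

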**Methods:**

A target of 894 SATURN participants will undergo a baseline MRI within 7 days of randomization and a repeat MRI at the end of the 24-month follow-up period. Any SATURN subject without contraindication to MRI has the option to participate in SATURN MRI. MRIs will be reviewed by blinded central raters to assess for the presence and burden of markers of CSVD and their progression. The primary outcome is new cerebral microbleeds and/or sulci with cortical superficial siderosis identified on T2*-weighted (GRE, SWI or SWAN) images between baseline and end-study MRI. Additional outcomes include the progression of white matter hyperintensity and incidence of covert infarcts.

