### Imaging analyses

Experienced readers, blinded to clinical details including treatment assignment, at the imaging core lab at the Seaman Family MRI Center at the University of Calgary will analyze the images. FDA compliant OsiriX software (Pixmeo SARL, Geneva, Switzerland) will be used to view the images. All incident lesions will be defined according to consensus guidelines for CMBs detection and STRIVE [15]. CMBs will be categorized by number (0, 1–2, 3–10, or > 10) and location (lobar, deep, or mixed deep/lobar), while cSS will be categorized as focal (involving ≤ 3 sulci) or disseminated (if involving ≥ 4 sulci). Covert infarcts will be defined as lesions in a vascular territory that are hyperintense on T2-weighted or FLAIR and hypointense on T1-weighted images, and if subcortical, they need to be at least 3 mm in size and have a round or ovoid shape to distinguish them from a perivascular space. Infarcts will furthermore be classified by size (> 15 or ≤ 15 mm axial diameter) and location (including cortical vs. subcortical and by lobe). Dilated perivascular spaces (Virchow-Robin) will be distinguished from infarcts on the basis of location, morphology, diameter (generally < 3 mm), and the absence of gliosis. Diffusion-weighted (DWI) hyperintense lesions will be defined as remote areas outside of the perihematomal border that are hyperintense on DWI with either corresponding hypointensity or isointensity on acute diffusion coefficient (ADC) sequences. White matter hyperintensities (WMH) will be divided into periventricular or deep and rated visually using the Fazekas scale. Semi-automated quantitative measurement of WMH volume will also be carried out using a Lesion Extraction Tool (University of Calgary; Calgary, AB, Canada).

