### Study outcomes

The primary outcome is new CMBs and/or sulci with cSS on T2*-weighted (GRE or SWI) images at end-study compared to baseline. Additional outcomes include the count of new CMBs, progression of WMH, and incidence of covert new non-lacunar infarcts between baseline and end-study MRIs. Clinical outcomes of (i) recurrent ICH, (ii) MACCE, (iii) cognitive decline (telephone T-Montreal Cognitive Assessment T-MoCA; https://mocacognition.com/), and (iv) poor functional outcome (modified Rankin Scale (mRS) 4–6) [16, 17] will also be assessed to determine if their relationship with statin use is modified by the presence and burden of CMBs and cSS on baseline MRI. The details on how functional and cognitive outcomes are assessed and collected are described elsewhere [14].

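### The ischaemic secondary outcomes are described inconsistently: lacunes are excluded in one section only, and WMH progression, measured by grade and volume, is analysed as presence of new markers

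*Protocol article*

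**What the plan says.** **Infarcts.** The Study outcomes section lists, among the additional outcomes, "progression of WMH, and incidence of covert new non-lacunar infarcts between baseline and end-study MRIs". The Methods part of the abstract puts it without the lacunar limit: "Additional outcomes include the progression of white matter hyperintensity and incidence of covert infarcts". The second item under Secondary objectives also has no limit: "the incidence of new ischemic MRI markers (white matter hyperintensities (WMH) and covert infarcts) on end-study MRI". The section on analyses for the secondary aims uses the same general terms. The reading rule under Imaging analyses says of covert infarcts that "if subcortical, they need to be at least 3 mm in size and have a round or ovoid shape", and then sorts them by axial diameter (above 15 mm, or 15 mm and below) and by location.

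**WMH.** The abstract and Study outcomes both name the outcome as progression. Imaging analyses provides two graded measures. WMH "will be divided into periventricular or deep and rated visually using the Fazekas scale", and in addition "Semi-automated quantitative measurement of WMH volume will also be carried out". The objective and the analysis section speak instead of new markers, and the one analysis given for the treatment effect on WMH and covert infarcts is that it "will be evaluated via logistic regression model relating the presence of new markers to treatment assignment".

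**Covariates.** Under Data analyses, all models are adjusted for the randomisation covariates: statin dose and indication, antithrombotic use, and severity of the enrolling haemorrhage. Baseline WMH is not among them.

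**The concern.** There are two separate problems.

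1. *Infarcts.* Whether a new lacune counts as an event depends on the section one follows. The Introduction lists lacunes among the markers of small vessel disease, and the study is about progression of those markers, so this is not a marginal class of lesion. Two analysts working from the same article could build different event indicators.

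2. *WMH.* WMH is a graded burden. For a patient who already has WMH at baseline, presence of new WMH could mean a rise in Fazekas grade, a rise in volume beyond some threshold, or a new separate focus. The article does not say which. It also fixes a binary model for a quantity that the core lab measures as a volume at both scans, with no stated adjustment for the baseline value.

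At stake is the interpretation of the ischaemic side of the study. The Discussion raises the possibility that statins reduce covert infarcts and WMH. A null result from an imprecise binary outcome could be taken as absence of benefit.

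**Working it through.** The article gives no event rate, effect size or power for WMH or covert infarcts, so there is no figure of the plan's own to reproduce. The main check sets the sections side by side.

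| Section | Infarct outcome | WMH outcome |
|---|---|---|
| Abstract, Methods | covert infarcts, no lacunar exclusion | progression |
| Secondary objectives | covert infarcts, no lacunar exclusion | new |
| Imaging analyses (reading rule) | subcortical lesions from 3 mm admitted; classes ≤ 15 and > 15 mm | Fazekas grade and volume |
| Study outcomes | non-lacunar only | progression |
| Analyses for the secondary aims | covert infarcts, no lacunar exclusion | presence of new markers, logistic model |

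For infarcts, only Study outcomes excludes lacunes, and the reading rule counts lesions of that size. For WMH, the outcome name (progression) and the measurements (grade, volume) point one way, while the objective and the model point another.

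**What a binary WMH outcome could cost (illustration).** Assumptions, none from the article: the change in suitably transformed volume is near normal, the treatment effect is a uniform shift, and the binary outcome is a cut of that same change.

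With event rate p, corresponding normal quantile z and standard normal density φ, the share of information kept is φ(z)² / [p(1 − p)].

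- p = 0.50: 0.3989² / 0.25 = 0.637
- p = 0.20: 0.490
- p = 0.10: 0.1755² / 0.09 = 0.342
- p = 0.05: 0.224

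**The same point as power.** The sample size section gives 652 evaluable subjects, so 652 / 2 = 326 per arm at 1:1. It does not state alpha; two-sided 0.05 is assumed. A continuous analysis then has 80% power for a standardised difference of (1.960 + 0.842) × √(2/326) = 0.219. The same shift, cut at different reference-arm rates, gives:

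| Reference-arm rate | Other-arm rate | Power, 326 per arm | Total for 80% power |
|---|---|---|---|
| 50% | 41.3% | 60% | 1032 |
| 30% | 22.9% | 54% | 1192 |
| 20% | 14.4% | 47% | 1442 |
| 12% | 8.2% | 37% | 1928 |

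The two calculations agree: 652 / 1032 = 0.63 against 0.637 at 50%, and 652 / 1928 = 0.34 against 0.342 at 10%, which lies between 12% and 8.2%. These figures concern WMH only and say nothing about infarcts.

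**The case against.** The strongest reply is that this is a condensed article, and that the analysis plan, which is not shown, may settle everything. Study outcomes is the one section whose purpose is to define outcomes. The abstract, the objective and the one-line model description may simply use a shorter label. For WMH, a rise in Fazekas grade is an obvious yes/no reading of progression, and volume might define the binary indicator or be analysed separately. Volume is also noisier when scanners range from 1.5 to 3.0 T. The carry-forward rule under Lost-to-follow-up and missing data is built for a binary indicator. These are secondary outcomes, and the stated directional hypothesis is the haemorrhagic one.

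Much of this stands. A reader might infer that the plan throws the WMH volume away. The documents do not show that; they show only that no stated analysis uses it as a continuous outcome. A reader might also infer that most of the sample is effectively lost for WMH. That is not supported either, because the efficiency figures rest on assumed normality, an assumed pure shift and assumed event rates, and they take no account of scanner differences. Nor do the documents show that the infarct definition will be chosen after the data are seen. Finally, the explicit non-lacunar definition may be the intended one, so it should not be overridden from outside.

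What the reply does not remove is the disagreement within the current text. The article does not leave the WMH model open; it names one, on an outcome worded differently from the outcome it defines. And its reading rule admits infarcts that its outcome definition excludes.

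**Conclusion.** The point holds as an inconsistency in the stated outcomes, together with a WMH analysis that, as written, is less precise than the collected data would allow. The infarct part rests on the text alone and needs no assumption. Its numerical effect is unknown, because the article gives no lacunar or non-lacunar rates.

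The size of the WMH part is illustrative. Under near-normal change and a shift effect, a binary outcome keeps about 64% of the information at a 50% event rate and about 34% at 10%. Other distributions or effect patterns would give other values.

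The primary outcome and its sample size are not affected. The change is worth making before analysis, at the level of a recommended revision.

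**What to change.** 1. *Infarcts.* Use one definition in the abstract, Secondary objectives, Study outcomes and the analysis section, stating whether lacunes count. The study team should choose. Whichever is chosen, report lacunar and non-lacunar components, derived by a written rule from the size and location data already read. Keep logistic regression for incident covert infarcts.

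2. *WMH.* Analyse end-study volume, suitably transformed, by a linear model adjusted for baseline volume and the randomisation covariates. As support, define a Fazekas grade increase and analyse it by logistic regression. Word the objective as progression, to match.

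3. *Missing data.* Carrying forward a new-marker indicator from an early clinical MRI has no counterpart for volume. State that early or missing volumes will be imputed on the continuous scale.

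The cost is small. It is mainly wording plus the additional imputation model. No new scans or readings are needed, since Imaging analyses already provides for volume, Fazekas grade, and infarct size and location.

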### Intervention

Participants will undergo a standardized brain MRI protocol during hospitalization within 7 days of randomization into SATURN and again within 30 days of the 24-month end-of-study period. Subjects who already undergo a baseline MRI as part of institutional practice are not required to undergo a repeat baseline study-specific MRI to participate in SATURN-MRI, provided that the MRI complies with the study imaging protocol (Table 1).

**Table 1 Tab1:** SPIRIT figure

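### The exploratory sex and race/ethnicity extension of the recurrent-ICH hazard model uses lesions known only near month 24; it should use baseline CMBs/cSS

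*Protocol article*

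**What the plan says.** All references are to the Protocol article.

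- **Base model** (Analyses related to the secondary aims). A proportional hazards model is used to "relate the time to symptomatic ICH recurrence to treatment assignment, the presence and burden of CMBs/cSS, and the corresponding interaction". The sentence opens by placing the markers on the baseline MRI.
- **Extension** (same paragraph). To explore heterogeneity across subgroups, that model gains main effects for sex and race/ethnicity and "their corresponding interactions with treatment and presence/number of new lesions".
- **What a new lesion is** (Study outcomes). The primary outcome is "new CMBs and/or sulci with cSS on T2*-weighted (GRE or SWI) images at end-study compared to baseline".
- **When it is known** (Intervention). The second MRI is done "again within 30 days of the 24-month end-of-study period".
- **Cognition and function** (Analyses related to the secondary aims). Mixed models for T-MoCA and mRS are built "in order to relate outcome to treatment, time, and presence of new lesions". Cognitive decline is a "reduction of at least two points from the highest score to any subsequent assessment". Poor function is mRS 4–6, which includes death.
- **Event-triggered MRI** (Lost-to-follow-up and missing data). If a participant has a stroke or recurrent ICH and cannot return, a compliant clinical MRI may stand in for the end-study MRI. A positive reading is carried forward. A negative one taken more than 3 months early is set to missing, and missing marker data are multiply imputed.

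**The concern.** A hazard model compares, at each event time, participants who have the event with those still at risk, using covariates known by then. New-lesion status is not known until about month 24, when the follow-up for recurrence is ending. Entering it as though known at randomisation has two consequences.

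First, the direction of effect is open. If a recurrent ICH makes later CMBs or siderosis more likely, the model will show lesions predicting recurrence even when they have no such effect. Second, the recurrence changes how the covariate is obtained, because the event can trigger the MRI that is read, and positive and negative readings are then kept by different rules.

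The extension also does not fit its base model. It interacts subgroup terms with a variable that the base model does not contain. At stake is the reading of any sex or race/ethnicity heterogeneity involving lesions.

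The cognitive and functional models raise the same issue to a lesser degree. Decline can be met at an assessment before month 24, and a participant who has died cannot have a month-24 MRI. Because the model contains a post-randomisation variable that is also the study's primary outcome, its treatment coefficient is not the randomised effect.

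**Working it through.** The plan gives no figure for this point, so the check is first of timing and then of possible size.

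**Timing.** Recurrences accrue from randomisation to month 24. Lesion status is fixed within 30 days of month 24, or at an earlier clinical MRI prompted by the event. In the section on the primary objective, new lesions are the outcome found on the end-study MRI, so the term has the same meaning there.

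**Inputs for size.** Sample size calculations gives 12% with new lesions over 24 months on discontinuation and, with the 8-point increase, 20% on continuation. These are the rates behind the stated 652. With two-sided alpha 0.05 (assumed) and 80% power:

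n per arm = [1.96·√(2·0.16·0.84) + 0.8416·√(0.12·0.88 + 0.20·0.80)]² / 0.08² ≈ 329, or 658 in total, within 1% of 652.

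The document gives no recurrent-ICH rate; 4% and 7% per year are assumed. The true effect of lesions on recurrence is set to a hazard ratio of 1.0.

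**Hand check.** Suppose recurrence occurs at month 12 and multiplies the later lesion hazard by k. With S the 24-month lesion-free probability without recurrence, the lesion probability after recurrence is 1 − S^((1+k)/2). Because recurrence is uncommon, the odds ratio approximates the spurious rate ratio.

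- Discontinuation, S = 0.88, reference odds 0.12/0.88 = 0.136:
  - k = 1: odds ratio 1.0
  - k = 2: 0.88^1.5 = 0.8255, odds 0.2114, ratio 1.55
  - k = 3: 0.88² = 0.7744, odds 0.2913, ratio 2.14
- Continuation, S = 0.80, reference odds 0.25:
  - k = 2: 0.80^1.5 = 0.7155, odds 0.3976, ratio 1.59
  - k = 3: 0.80² = 0.64, odds 0.5625, ratio 2.25

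**Simulation.** N = 894, 150 replicates per setting. A Cox model included treatment and the end-study lesion indicator entered as a baseline covariate. The last column adds the event-MRI rule, assuming 30% of recurrences are fatal and 20% of all recurrences have only an event MRI. It is analysed as complete cases.

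| Later accrual multiplied by | All have month-24 MRI (4% / 7% per year) | With event-MRI rule (4% / 7% per year) |
|---|---|---|
| 1 | 0.94 / 0.99 | 1.16 / 1.21 |
| 2 | 1.48 / 1.50 | 1.75 / 1.73 |
| 3 | 2.10 / 2.12 | 2.32 / 2.28 |

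The hand check and the first simulation column agree closely. Two limits apply. The plan uses multiple imputation, not complete cases, so the last column is a guide only. The figures are for the lesion main effect, whereas the plan's sentence concerns subgroup interactions, so they show that the covariate can mislead but do not measure bias in the planned contrast.

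**The case against.** The strongest reply is that the fault sits in one exploratory sentence, and that its wording may be a slip for baseline lesions, since the model being extended uses them. That is plausible and limits the severity. The sentence still needs correcting, because elsewhere the article uses the term for incident lesions.

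For cognition and function, Secondary objectives places the aim at 24 months and speaks of marker accrual, and the analysis section calls it an association. New lesions therefore belong in that analysis, and at month 24 the two are concurrent. Nothing in the article presents the treatment coefficient there as the randomised effect. What stands is the use of earlier assessments and of death.

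A reader might infer three stronger things that the document does not support.

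- **That the baseline-marker interactions are omitted.** The interaction for recurrent ICH is specified and sound. Study outcomes lists four clinical outcomes to be assessed "to determine if their relationship with statin use is modified by the presence and burden of CMBs and cSS on baseline MRI", and Secondary objectives says "We also aim to examine the modifying effects of these markers on the risk of MACCE". No model with that interaction is written for MACCE, cognition or function, but a condensed article may leave those to an analysis plan that is not shown. Silence is not contradiction.
- **That those who die of a recurrence never contribute an MRI.** The section on missing data allows a compliant clinical MRI at the event to serve, and imputes the rest. This does not remove reverse causation and may add to it, but the absolute statement is wrong.
- **That the distortion is known to be large.** Assuming outright that 20%, 30% or 40% of participants with recurrence show new lesions gives ratios of 1.8 to 4.4. Those percentages come from outside the document.

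**Conclusion.** The point holds in a limited form. Followed literally, the subgroup extension of the recurrent-ICH model conditions on information obtained after the event, allows reverse causation, and does not match its base model. This conclusion follows from the document's own timing and needs no outside figure.

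The size does need outside figures. It depends on assumed recurrence rates and, above all, on whether recurrence speeds lesion accrual. If it does not, and all participants have the month-24 MRI, there is little bias. If it doubles or triples accrual, a null association can look like a hazard ratio of about 1.5 to 2.3.

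The T-MoCA and mRS models have a lesser version of the problem, confined to assessments before month 24, deaths, and any causal reading of the treatment term.

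This should be fixed, but it does not threaten the trial's main conclusions. The primary analysis and the treatment-by-baseline-marker model for recurrent ICH are unaffected.

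**What to change.** 1. In the sex and race/ethnicity extension of the proportional hazards model, replace new lesions with baseline CMB/cSS presence and burden, so that it matches the model it extends.
2. Restrict the new-lesion association with T-MoCA and mRS to status at 24 months, as Secondary objectives words the aim. State how participants who died before the end-study MRI are handled, and that the treatment coefficient in this model is not an estimate of the randomised effect.
3. As a clarification only, say where the baseline-marker interaction models for MACCE, cognition and function are specified.

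The cost is wording. The baseline markers and the 24-month outcomes are already being collected, and the sample size and primary analysis do not change. The change is best made before outcome data are examined.
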